### Statistical analysis

The effect of group allocation on continuous outcomes will be assessed using linear regression models in which pre-test performance is a covariate. The number of falls per person-year will be analysed using negative binomial regression to estimate the between-group difference in fall rate [43]. The difference between the proportions of fallers in each group will be calculated using the relative risk statistic. Longitudinal analyses will be used to assess the effects on the variables measured each 3 months. Logistic regression models will be used to compare groups for dichotomous outcomes. Additional regression analyses will establish predictors for program adoption and adherence and cost-effectiveness. Sub-group analyses will be conducted using only participants with hip fracture to enable these data to be used in systematic reviews. Data will be coded to permit blinding to group allocation in the statistical analysis and the primary analyses will be conducted in accordance with the intention-to-treat principle [44]. Analyses will be conducted using the Stata software package, College Station, Texas.

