### Data collection

Data will be collected from medical records (where possible), participant interviews in person and by telephone, physical assessments, and calendars mailed to the research centre. Participants will undergo two home-based assessments; one prior to randomisation and the other 12 months after randomisation. A physiotherapist or a trained research assistant who is unaware of group allocation will perform the assessments. Each assessment will take about one hour to complete.

Details of fracture, comorbidities and hospital stays will be obtained from the medical records where possible. From participant interviews we will obtain baseline information on pre-fracture daily task independence, fracture details, medical conditions, cognition (using the Short Portable Mental Status Questionnaire) [33], nutrition (Mini Nutritional Assessment) [34], medications, and fracture interventions (including surgical fixation, occupational therapy home visits and physiotherapy). The primary and secondary outcomes will be administered at baseline and 12-month assessments.

All participants will receive 12 one-month calendars and questionnaires at the time of the baseline assessment. Participants will be asked to record falls (primary outcome) and use of health and community services on the calendars and to return completed calendars in pre-paid envelopes to the research centre each month. If calendars are not returned, participants will be telephoned to ask about their fall history for that month. Any fall reported on the calendars will be followed up with a phone call to obtain further information about the details and consequences of the fall. All participants will be telephoned at three, six, nine and twelve months for assessment of the Boston University Activity Measure for Post Acute Care (AM-PAC; primary outcome) [35], and European Quality of Life-5 dimensions quality of life assessment (EQ-5D-5 L; secondary outcome) [36]. Staff who receive calendars and questionnaires, make follow up phone calls and enter data will be unaware of group allocation.

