Physical activity	Incidental and Planned Exercise Questionnaire [57]	Level of physical activity relating to both basic and more demanding activities is assessed with a 10-item questionnaire.
Walking aid use	Use of walking aid	The use and type of walking aid is recorded both indoors and outdoors.
Frailty	6-point scale based on the Fried criteria [58]	Frailty is measured using five criteria: unexplained weight loss, grip strength, exhaustion, walking speed, activity level.
Pain	6-point numeric rating scale	The participant selects a whole number that best reflects the intensity of their pain.
Nutritional status	Mini Nutritional Assessment [34]	Screens for, and assesses, malnutrition in older people.
	Body mass index	Bodyweight in kilograms divided by height in metres squared.
Fall-related self-efficacy	Questions about self-rated fear of falling and balance	Participants are asked to rate their perceived balance and their fear of falling on 5-point ordinal scales
	Short version of the Falls Efficacy Scale-International [59]	Level of concern about falling during a range of activities is rated on a 4-point scale.
Mood	Five-item version of the Geriatric Depression Scale [60]	Screens mood in older people. The five-item Geriatric Depression Scale is comparable with the 15-item version in terms of psychometric properties.
Positive and negative affect	Positive and Negative Affect Scale [61]	Two 10-item scales that measure positive and negative affect.
Health-related quality of life	European Quality of Life-5 dimensions (EQ-5D-5 L) [36]	A standardised measure of health status that provides utility weights to allow calculation of quality adjusted life years (QALYs) for use in the economic evaluation [62].
	Short Form 12-item Survey (SF-12) Version 2 [63]	A 12-item questionnaire that measures functional health and well-being.
Assistance from others	Three questions about assistance received	Establishes the presence of, and reason for, assistance from agencies, family or friends.

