### Sample size calculation

A total of 350 participants (175 per group) will be recruited. The study will have 80 % power to detect as significant, at the 5 % level, a 30 % decrease in the rate of falls (i.e. an IRR of 0.70 using negative binomial regression analysis) over the 12-month study period. This sample size will provide 90 % power to detect a statistically significant between-group difference of 10 % in lower extremity continuous summary performance score [46] For these calculations, we assumed an α of 0.05, non-compliance of 15 % and a dropout rate of 15 %.

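### Baseline adjustment is stated for continuous outcomes only; naming baseline status in the logistic models would be a free and possibly useful gain in precision for dichotomous secondary outcomes

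*Protocol article*

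**What the plan says.** The Statistical analysis section of the protocol article treats the two kinds of outcome differently. Continuous outcomes go into "linear regression models in which pre-test performance is a covariate". Later in the same paragraph the binary outcomes get one sentence: "Logistic regression models will be used to compare groups for dichotomous outcomes". The proportion of fallers is handled separately, by a relative risk.

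The Data collection section states: "The primary and secondary outcomes will be administered at baseline and 12-month assessments". Table 1 of secondary outcomes contains two entries that are natural candidates for the logistic sentence:

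- Walking aid use: "The use and type of walking aid is recorded both indoors and outdoors".
- Assistance from others: "Establishes the presence of, and reason for, assistance from agencies, family or friends".

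Both are listed among the secondary objectives. The article does not define how either is to be made dichotomous.

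**The concern.** An analyst who fitted a logistic model with treatment group alone would be following the text as written. The paragraph names the baseline covariate where it is wanted for continuous outcomes and names none for binary ones.

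In this population the baseline value could matter. The fracture may be up to two years old, and people still in a rehabilitation program are excluded, so many participants may have a settled pattern of aid use or help. If so, status at entry would predict status at 12 months, and leaving it out would discard information already collected. The Randomisation and blinding section describes permuted blocks and mentions no stratification, so nothing stated in the article balances these features between arms.

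What is at stake is the width of the confidence intervals for secondary measures of disability. The primary analyses and the validity of the tests are not affected.

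**Working it through.** **The plan's own figures.** The Sample size calculation section gives "A total of 350 participants (175 per group) will be recruited". Its power statements concern the fall rate and the performance score. None is made for a dichotomous outcome, so there is no stated figure to reproduce.

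**Inputs from the article.** 175 per arm and 15% dropout: 175 × 0.85 = 148.75, taken as 149 per arm.

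**Assumed inputs, not in the article.** Prevalence 50% at baseline in both arms; 50% in control and 35% in intervention at 12 months (a 15-point effect); phi of 0.1, 0.3 or 0.5; two-sided 5% test. The probability of the outcome at 12 months is

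0.5 + phi × (baseline − 0.5) − 0.15 × group, with baseline and group coded 0 or 1.

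**Step 1, no baseline term.**

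SE = √[(0.5 × 0.5 + 0.35 × 0.65)/149] = √(0.4775/149) = 0.0566.

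0.15/0.0566 = 2.65, and power = Φ(2.65 − 1.96) = 75%.

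**Step 2, with baseline status.** Within each arm, the variance p(1 − p) is averaged over the two baseline groups. This is a large-sample approximation on the risk-difference scale.

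| phi | Control p (baseline yes / no) | Intervention p (baseline yes / no) | Sum of average variances | SE | Power |
|---|---|---|---|---|---|
| 0.1 | 0.55 / 0.45 | 0.40 / 0.30 | 0.2475 + 0.2250 = 0.4725 | 0.0563 | 76% |
| 0.3 | 0.65 / 0.35 | 0.50 / 0.20 | 0.2275 + 0.2050 = 0.4325 | 0.0539 | 80% |
| 0.5 | 0.75 / 0.25 | 0.60 / 0.10 | 0.1875 + 0.1650 = 0.3525 | 0.0486 | 87% |

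**Step 3, simulation of the logistic Wald test under the same assumptions.**

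- phi = 0.1: no gain.
- phi = 0.3: about 76% without and 78% to 79% with baseline status, a gain of 2 to 3 points.
- phi = 0.5: about 75% to 76% without and 86% with, a gain of 10 to 11 points.

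The approximation in step 2 is about a point higher in each gain. With 4,000 trials the Monte Carlo standard error of one power figure is √(0.75 × 0.25/4000) = 0.7 points, so the two agree.

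**Step 4, a different parameterisation.** The control rate is again 50%, with 34% on intervention, and the baseline-outcome association is set as an odds ratio. Power without and with baseline status is 82% and 81% at an odds ratio of 1, 81% and 82% at 3, 80% and 90% at 10, and 80% and 96% at 30. For comparison, phi = 0.5 in step 2 is an odds ratio of (0.75/0.25)/(0.25/0.75) = 9 in controls. The gain is material only when baseline status is strongly prognostic.

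**Step 5, validity.** With no treatment effect, rejection stays near 5% in both models: 4.6% to 6.4% unadjusted and 4.3% to 5.8% adjusted over the scenarios of step 4, with Monte Carlo error of about 0.5 points.

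**Step 6, chance imbalance.** The baseline difference between arms has SD √(2 × 0.25/149) = 0.058, or 5.8 points. At phi = 0.5, a 2-SD imbalance of 11.6 points would move the crude 12-month difference by 0.5 × 11.6 = 5.8 points. An imbalance that large arises in about 5% of trials, and the unadjusted standard error already allows for it.

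**The case against.** The strongest case against is that the article is silent here and has not made a wrong choice. The logistic sentence names a model family; it neither lists covariates nor excludes them, and comparing groups describes an adjusted model as well as an unadjusted one. A full protocol or analysis plan that is not shown may name the covariate. Table 1 records the type of walking aid as well as its use, and the reason for assistance as well as its presence, so it is an inference that these outcomes enter the logistic model in yes/no form. The prevalence, effect and phi are all assumed.

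Much of this stands. A reader might infer that the trial has decided to leave baseline status out, that these outcomes will therefore lose power, or that chance imbalance will bias them. The article supports none of these. It does not exclude covariates; the power loss depends on an association it does not give and is nil if that is weak; and an unadjusted randomised comparison keeps its type I error.

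What remains is narrower. The paragraph does not leave covariates wholly to another document: it commits to a baseline covariate for one kind of outcome and states the other without one. Following it literally gives an analysis that is at best as efficient as the adjusted one when baseline status predicts the outcome.

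**Conclusion.** The point holds as a minor improvement. As worded, the logistic models carry no baseline term, while baseline status is due to be collected for the outcomes they most plausibly serve. The unadjusted comparison would be valid but may be less precise. The gain in power from adjustment is about 0 points at phi 0.1, 2 to 3 at phi 0.3 and 10 to 11 at phi 0.5. These sizes rest on an assumed 50% prevalence, an assumed 15-point effect, 149 per arm after the stated dropout, and a yes/no coding that the article does not define. Only secondary outcomes are involved, and no stated sample size, power figure or primary conclusion changes.

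**What to change.** Extend the logistic sentence in the Statistical analysis section along these lines: dichotomous outcomes measured at baseline, such as walking aid use (yes/no, indoors and outdoors) and presence of assistance, will be compared by logistic regression including the baseline status of that outcome as a covariate. If an analysis plan already says so, a cross-reference is enough.

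The cost is one sentence and one model term, using data the trial already plans to hold. The adjusted odds ratio is conditional on baseline status and will generally differ from the crude one. A standardised risk difference with its 95% confidence interval may be reported alongside to ease reading, but this is optional.

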### Economic evaluation

The economic evaluation will be conducted and reported in accordance with international reporting standards [45]. The economic evaluation will take the perspective of Australian health and community care funder. The cost-effectiveness analyses will include the cost of delivering the intervention (staff, training, capital costs and consumables), inpatient hospital admissions, emergency department presentations and other health and community service contact, falls rates, mobility and utility based quality of life. Incremental cost-effectiveness ratios will be calculated in terms of 1) fall prevented, 2) hospital re-admission avoided, 3) participant achieving a significant increase in mobility (one point on the SPPB [46]), and 4) QALY gained in the intervention group compared with control group, using the mean health outcomes and the mean costs in each trial arm. Bootstrapping will be used to examine the joint probability distribution of costs and outcomes; incremental cost-effectiveness planes and cost-effectiveness acceptability curves will be reported for each outcome.

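### The cost-per-QALY ratio is built from arm means with no adjustment named for baseline EQ-5D utility, which costs precision and lets part of any chance baseline difference into the incremental QALYs

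*Protocol article*

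**What the plan says.** The Economic evaluation section lists four incremental ratios: per fall prevented, per readmission avoided, per participant with a one-point SPPB gain, and per QALY. All are to be calculated "using the mean health outcomes and the mean costs in each trial arm". For uncertainty, "Bootstrapping will be used to examine the joint probability distribution of costs and outcomes". No covariate is named.

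The utilities come from the EQ-5D-5L, which according to Table 1 "provides utility weights to allow calculation of quality adjusted life years (QALYs) for use in the economic evaluation". The Data collection section gives its timing. It is a secondary outcome, and "The primary and secondary outcomes will be administered at baseline and 12-month assessments". In addition, "All participants will be telephoned at three, six, nine and twelve months for assessment of the" AM-PAC and the EQ-5D-5L. A baseline utility and four follow-up values are therefore planned.

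For the clinical analysis, the Statistical analysis section specifies "linear regression models in which pre-test performance is a covariate" for continuous outcomes. It does not extend that rule to QALYs. Its one mention of cost-effectiveness concerns regressions to find predictors.

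**The concern.** A 12-month QALY is usually an area under a utility curve that begins at the baseline value, and a person's later utilities correlate with that value. If one arm happens to start with higher utility, part of that head start appears in its mean QALYs although the intervention did not produce it. The plan guards against this for its continuous clinical outcomes but, as written, not for the QALYs.

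Cost-utility is a stated secondary objective. The cost-per-QALY ratio divides by a QALY difference that may be small, so a modest shift in that difference can change the ratio and the acceptability curve noticeably.

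**Working it through.** The article gives no precision or power figure for QALYs or for any ratio, so there is no stated figure to reproduce.

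**Inputs from the article**
- Sample size: "A total of 350 participants (175 per group) will be recruited".
- Losses: "we assumed an α of 0.05, non-compliance of 15 % and a dropout rate of 15" per cent. Participants with complete data: 175 × 0.85 = 148.75, about 149 per arm.
- EQ-5D-5L at 0, 3, 6, 9 and 12 months.

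**Assumptions (not in the article)**
- QALYs by the trapezoid rule.
- Utility SD 0.15 to 0.25, the same at each visit.
- Correlation r between baseline and each later visit of 0.5 to 0.7. For the precision check, r holds between all pairs of visits.
- A true gain of 0.02 QALY, used for illustration.

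**Step 1: share of a baseline difference that carries through.** The trapezoid weights are 0.125, 0.25, 0.25, 0.25 and 0.125. The baseline value enters directly with weight 0.125, and the later values, with total weight 0.875, follow it in proportion r. Share = 0.125 + 0.875r.
- r = 0.5: 0.5625, about 56 %
- r = 0.6: 0.65
- r = 0.7: 0.7375, about 74 %

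**Step 2: likely size of a chance imbalance.** SE of the baseline difference = SD × √(2/148.75) = SD × 0.116.
- SD 0.15: 0.017
- SD 0.20: 0.023
- SD 0.25: 0.029

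**Step 3: shift in incremental QALYs** (share × imbalance).

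| Case | 1-SE imbalance | 1.96-SE imbalance |
|---|---|---|
| SD 0.15, r 0.5 | 0.010 | 0.019 |
| SD 0.20, r 0.6 | 0.015 | 0.030 |
| SD 0.25, r 0.7 | 0.021 | 0.042 |

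In the middle case, imbalance alone would cancel a true gain of 0.02 if it reached 0.02/0.015 ≈ 1.33 SE in the unfavourable direction, a chance of about 9 %. For a true gain of 0.01 the chance is about 25 %, and for 0.03 about 2 %.

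**Step 4: precision, whatever imbalance occurs.** The squared weights sum to 2 × 0.125² + 3 × 0.25² = 0.21875. In units of SD², with r = 0.6:
- QALY variance, unadjusted: 0.4 × 0.21875 + 0.6 = 0.6875
- QALY variance given baseline utility: 0.6875 − 0.65² = 0.265

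With SD 0.20 and 149 per arm, the SE of incremental QALYs is:
- unadjusted: 0.20 × √(0.6875 × 2/149) = 0.0192
- adjusted: 0.20 × √(0.265 × 2/149) = 0.0119

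With a true gain of 0.02, the overall chance of a wrong-signed QALY difference falls from about 15 % to about 5 %. At the full 175 per arm, the SE falls from 0.0177 to 0.0110 and the chance from about 13 % to about 3.5 %.

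**Step 5: simulation.** In 5,000 simulated trials (175 per arm, SD 0.20, r 0.6, true gain 0.02), both estimators averaged 0.020. The slope of the estimate on the baseline imbalance was 0.65 unadjusted and about 0.00 adjusted. This confirms unbiasedness on average, the share in Step 1, and that regression on baseline utility removes the dependence.

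**The case against.** The strongest reply is that the article never says the means are unadjusted. Regression-adjusted means are still arm means, the wording may only fix the ratio as one of mean differences, and a condensed article leaves covariates to an economic analysis plan. The trial's general policy also favours adjustment, with a pre-test covariate for continuous outcomes and longitudinal models for three-monthly measures.

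Part of this stands: simple means are the most natural reading, but an inference. It does not dispose of the point. The section is not silent; it states its own estimator. The pre-test rule does not transfer by itself, because a QALY has no pre-test value of its own, and the regressions for predictors of cost-effectiveness answer another question.

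Four stronger readings are tempting, and the documents do not support them:
- *The ratio is biased.* Participants are randomised, so the unadjusted difference is unbiased on average. The issue is lost precision and an imbalance in the one trial that is run.
- *A baseline difference passes through whole.* Only 56 to 74 % does under the assumed correlations.
- *The bootstrap hides the problem.* Resampling participants includes the variance from chance imbalance, so the planned plane and acceptability curve would be wider, not falsely certain. They would still be centred on the imbalanced estimate.
- *All four ratios are affected.* Falls and readmissions have no utility baseline, and the SPPB outcome is already defined as an increase.

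The sizes also rest on assumed SDs, correlations and gain. A change of sign is plausible mainly when the true QALY gain is small.

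**Conclusion.** The point holds for the cost-per-QALY ratio. The stated estimator names no baseline adjustment, although the covariate is collected and the clinical analysis uses the same principle. The case for adjustment does not depend on an unlucky draw: in the middle case it lowers the standard error of incremental QALYs by roughly 38 % (1 − 0.0119/0.0192). The table in the working gives the cost of an unlucky draw under its stated assumptions. The primary outcomes are untouched. This is an improvement that should be made to a secondary analysis, not a flaw that invalidates it.

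**What to change.** In the Economic evaluation section, add a sentence to this effect for the cost-per-QALY ratio:

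> Incremental QALYs will be estimated by linear regression of QALYs on trial arm and baseline EQ-5D-5L utility. The regression will be refitted in each bootstrap sample, and incremental costs will be taken from the same resample so that the correlation between costs and QALYs is kept.

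A joint model such as seemingly unrelated regression is one way to do this, but it is not required. Leave the other three ratios as they are. If adjustment was always intended, the same sentence settles the ambiguity.

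The cost is wording and a few lines of analysis code. Baseline EQ-5D-5L is already in the assessment schedule, so no new data, visits or participants are needed. The sentence should be fixed before the arms are compared.

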### Process evaluation

A process evaluation will aim to quantify adherence, explore the participants’ experience of the intervention, and determine features associated with uptake of the intervention. This will be undertaken via calendars, verbal reports, questionnaires and a qualitative sub-study.

Adherence to the prescribed intervention will be monitored with home exercise diaries and verbal reports from participants in the intervention group. The total repetitions of home exercise performed will be divided by total repetitions prescribed. Global level of adherence will be estimated as a percentage. Participants will also be asked to identify reasons for adoption and adherence as well as non-adoption and non-adherence.

Participants’ experience of the intervention will be investigated using three questionnaires. A modified version of the Exercise Benefits/Barriers Scale [47] explores the perceived facilitators and barriers to exercise; five items measure the individual’s confidence in their ability to persist with exercising in various situations [48]; and nine questions explore the acceptability and enjoyment of the intervention.

In a subset of participants, a qualitative study will further explore the participants’ experiences of recovery from fall related fracture and participation in the study intervention program.

